### Follow-up

Male and female participants will be followed-up at the end of the intervention (approximately 4 months post-randomisation) (Table 2). Reminder telephone calls or texts will be sent in advance to arrange and confirm a time for follow-up interview.

**Table 2 Tab2:** Schedule of enrolment, interventions, and assessments

Study phase				
Timepoint	Screening	Baseline and randomisation	Intervention delivery	Follow-up
Enrolment:				
Informed consent	X	X		
Eligibility screen	X			
Baseline interview		X		
Allocation		X		
Follow-up interview				X
Interventions:			(16 weeks)	
Intervention + TAU				
TAU				
Assessments:				
Childhood		X		
Substance use	X (males only)	X		X
Mental health		X		X
Intimate partner abuse	X (males only)	X		X
Quality of life		X		X
Service use		X		X
Desirable responding		X (males only)		X (males only)
Motivation to change behaviour		X (males only)		
Self-management		X (males only)		X (males only)
Therapeutic alliance				X (males in intervention arm only)

### Method of randomisation

Male participants will be allocated to the intervention group+ substance use treatment as usual (TAU) or TAU only (ratio 1:1) by site via an independent online system based at the Clinical Trials Unit. Allocation will be at the level of the individual participant, using randomly varying block sizes, stratified by a combination of sites and cycles (18 participants per site/cycle stratum).

### Blinding

The statisticians will be blind to the trial condition throughout the feasibility trial. The health economists will not be blind to the allocation as the intervention costs will have to be assigned to the correct treatment arm. Researchers will not be blind to the group allocation of participants, as they will also be responsible for participant recruitment and reminder telephone calls to attend intervention sessions.

### Intervention arm

The TIDieR (Template for Intervention Description and Replication) Checklist was used to describe the intervention [38] (Additional file 1: Table S3). The Behaviour Change Wheel, incorporating the COM-B model (capability, opportunity, and motivation for behavioural interventions) was used to provide a framework to develop the ADVANCE intervention [39]. The ADVANCE intervention is voluntary, i.e. men are not mandated to attend by the court. Within the COM-B model, the intervention thus considered how capability, opportunity, and motivation for each could be addressed and which type of intervention would be best to enact each. Thus, modelling, enablement, education, incentivisation, and training are included in the intervention. In the ADVANCE intervention, capability is enhanced by increasing participants’ knowledge and skills based on the self-regulation model. In particular, awareness around crisis planning and self-management is raised and automatic thoughts and beliefs are challenged by evaluating the consequences. Opportunity is provided to model and promote positive behaviour within intervention sessions, and out-of-session tasks to generalise learning. Each week, sessions were reviewed to reinforce positive achievements. Finally, goal planning is used to motivate participants and reinforcement of motivation is achieved through ongoing personal support and incentives. The ADVANCE intervention is manualised comprising 2–4 individual sessions (2 need to be completed before beginning the group intervention) with a keyworker to set goals, develop a personal safety plan, and increase motivation and readiness followed by a 12-week group intervention (Fig. 2) ([name], [name], [name], [name], [name], [name]: Designing an implementation intervention with the Behaviour Change Wheel for Men in Substance Use Services who have been abusive to an intimate female partner, in preparation). Given the high level of trauma, family disruption, abuse, and neglect in this population, interventions targeting IPA in men who use substances require a trauma-informed approach [40]. Recent approaches with forensic populations indicate that strengths-based approaches, designed for a range of learning styles, avoiding shame and judgement are more effective [41, 42]. Three potential targets for effective IPA change were identified as reducing pro-abuse attitudes including locating causality for abuse in substance use, managing distress individually and pro-socially, and learning effective, non-abusive behavioural responses within relationship negotiations. The ADVANCE intervention focuses on developing participants’ strengths and developing healthy, non-abusing relationships. Two main models to enable change were selected (1) personal goal setting, to work with individual goals, and to build genuine motivation through alignment with personal values and facilitate change by breaking larger longer-term aims into specific small steps that can be more easily achieved, reinforcing motivation through these small achievements and (2) informed by the self-regulation model which suggests that building self-management in one domain enables more effective self-management across other domains. The intervention requires individuals to set specific goals for reducing risk, such as changing substance use, and for developing a prosocial lifestyle in terms of work, leisure, health, and accommodation. Underpinning the goal-focused approach is the need to improve self-regulation of behaviours, achieved by identifying and changing cues, appraisals (thoughts), emotions, behaviours, and consequences. Throughout the ADVANCE intervention, behaviour change skills are introduced and practised. The 12 group sessions will address the following:
Session 1. Introduction to the groupSession 2. Managing myselfSession 3. Behaviour analysis + genderSession 4. Impact of intimate partner abuseSession 5. Children, parenting, substance use + intimate partner abuseSession 6. RelatingSession 7. Improving communicationSession 8. Dealing with distressSession 9. Planning to be betterSession 10. Positive relationshipsSession 11. New futures, peoples plans + positive activitiesSession 12. Recap what we have learned

**Fig. 2 Fig2:**
[figure not shown]
ADVANCE intervention

Pre-group individual sessions will be delivered by keyworkers in substance use treatment service. The group intervention will also be delivered in substance use treatment services by two trained facilitators, where possible one female and one male. Keyworkers or facilitators will check-in by phone with participants between group sessions to address any issues arising during the session. Participants will be given out of session practice exercises. Facilitators will send a weekly feedback to participants’ keyworkers by email after each session to update them on progress, safeguarding issues and risk. Group sessions will be video recorded with participants’ consent and checked for fidelity. Only those consenting to being video recorded would be able to take part in the trial.

Fortnightly, integrity support meetings will be held with facilitators to discuss delivery issues and address any expected problems for delivery of the next two sessions. Four case management meetings will take place with facilitators (and keyworkers where possible) and the integrated safety service workers over the course of the intervention to consider risk. Aftercare is provided in the form of workbooks for men, keyworker guidance, and signposting.

Contingency management, recommended by the National Institute for Health and Care Excellence [43], will be used to encourage motivation and retention of participants in the group intervention by offering incentives to attend the ADVANCE integrated intervention. Participants in the intervention arm only will receive a £5 voucher (for a shop or service of their choosing) for attending each of the 12 sessions up to a total of £60. These will be awarded at session 6 and session 12 of the group intervention. If a participant attends all 12 sessions an additional £10 ‘bonus’ voucher will be available. Travel will also be reimbursed, and refreshments provided.

The integrated safety service will also contact the female current or former partners of males in the intervention arm on at least three occasions to update them on their current or ex-partner’s overall progress within the intervention. They will also contact women if there is anything that they need to know to keep themselves and their families safe.

### Control arm

Men in both treatment arms will receive substance use TAU including group work, individual sessions, mutual aid, and opiate substitution treatment. Integrated safety services and individualised support are offered to all participants’ female current or ex-partners as needed, regardless of the allocation to a group of their male partners.

Data from naturalistic studies found that the relative risk for IPA after substance use treatment was 2–3 times greater amongst those who relapsed compared to those who successfully completed treatment [44], potentially as a result of a reduction in alcohol use and improved relationship functioning. Therefore, the selection of substance use TAU as a comparator for this feasibility study is justified. Moreover, men’s keyworkers will be informed that their client has perpetrated IPA in the past 12 months regardless of group allocation and may choose to address this as part of TAU.

### Fidelity

All group intervention sessions will be video recorded with participants’ and facilitators’ consent. Facilitators’ fidelity of the delivery of the intervention manual will be assessed by a trained observer using a pre-defined checklist for each session of the intervention. Video recordings will allow the same observer to assess treatment integrity, the degree to which treatment is implemented as intended across sites. Sessions are videotaped for assessment of treatment fidelity, therapist skill, and competency in delivering the interventions and the discriminability of the study treatments. Treatment fidelity will be assessed using an adapted form of the Yale School of Medicine Adherence and Competence Scale [37], shown to be successful at discriminating key therapy content and skill domains [38]. A series of checklists are created to tap into key unique components of specific therapies (e.g. experimental condition vs. control) as well as a series of scales tapping common factors (e.g. assessment of substance use and general functioning).

### Formative evaluation

At the end of each group session, men will be asked to self-complete a brief evaluation form. Facilitators will complete a brief treatment adherence form after each session. All TAU contacts will be recorded by keyworkers for men (regardless of treatment arm). Integrated safety support workers will record contacts with the current or ex female partners of men in both treatment arms. Focus groups with staff at the end of each cycle of the intervention will examine their experiences of delivering the intervention. After completion of the first cycle of the intervention at each site, interviews with participants will explore their experiences and acceptability of attending the intervention and participating in the trial.

### Feasibility measures

The primary objective of this study is to demonstrate the feasibility of conducting a trial to evaluate the intervention, including the feasibility and acceptability of delivering the intervention in substance use treatment and the feasibility of outcome measure collection on perpetrators and their current or former female partners. The following feasibility parameters will be examined: rates of consent, recruitment, and follow-up by site and group allocation. The estimation of background variability will inform sample size calculations for a future evaluation trial.

Men’s TAU attendance for both treatment arms, attendance, and retention in the ADVANCE intervention for men allocated to the treatment arm, and numbers of current or former female partners accepting the offer of support from the integrated safety service will also be collected.

### Participant-centred outcome measures

The suitability and acceptability of outcome measures will be assessed to determine the feasibility of including them in a future effectiveness trial. Researchers’ perceptions of participants’ understanding (e.g. of language and meaning of questions) and acceptability (e.g. if participant refuses to answer or gets annoyed/frustrated or asks to end the interview) will be recorded for each outcome measure using a pre-determined rating scale (1—lowest rating to 3—highest rating for understanding and acceptability). The following outcome measures will be assessed at baseline for men and initial interview for women and at the end of the intervention (4 months post-randomisation of men) for men in both treatment arms and their current or former female partners (unless otherwise specified) (Table 2).

### Substance use

*The Alcohol Use Disorders Identification Test* (AUDIT) (included in the baseline questionnaire only) is a 10-item screening tool used to assess alcohol use in the past 12 months [45]. Scores range from 0 to 40. Total scores of 8 or more for men (7 or more for women) indicate hazardous and harmful alcohol use, and scores of 20 or above indicate alcohol dependence.

*The Drug Use Disorders Identification Test* (DUDIT) (included in the baseline questionnaire only) is an 11-item screening tool used to *identify drug*-related problems [46]. Scores range from 0 to 44. Total scores of 6 or more for men (2 or more for women) indicate drug-related problems, and scores of 25 or more indicate drug dependence.

As the AUDIT and DUDIT assess substance use in the past 12 months they will not be used to measure substance use outcomes post-intervention (4 months post-randomisation). Instead, the average amount on a using day and number of days substances used in each of the past 4 weeks will be recorded using the Treatment Outcome Profile [47] at baseline and follow-up. The number of days in the past 4 weeks that problems with particular substances were experienced will also be recorded using *The Addiction Severity Index* [48] as will current treatment for substance use.

### Mental health

*The Patient Health Questionnaire* (PHQ-9) is a 9-item scale measuring depressive symptoms in the past 2 weeks [49]. The total score ranges from 0 to 27. A score ≥ 10 has a sensitivity of 88% and a specificity of 88% for major depression.

*The Generalised Anxiety Disorder Assessment* (GAD-7) is a 7-item scale measuring general anxiety symptoms in the past 2 weeks [50]. The total score ranges from 0 to 21. A score of ≥ 10 represents a reasonable cut off point for identifying cases of GAD.

*The Primary Care Post-Traumatic Stress Disorder (PTSD) Screen* (PC-PTSD-5) is a 5-itccem screen for PTSD in the past month, with scores ranging from 0 to 5 [51]. A score of ≥ 3 indicates PTSD.

*The Standardised Assessment of Personality—Abbreviated Scale* (SAPAS) (included in male baseline questionnaire only) is an 8-item screening interview for personality disorder [52] enquiring about a person’s behaviour in general rather than a specific time frame. Scores range from 0 to 8. A score ≥ 3 correctly identified the presence of DSM-IV personality disorder in 90% of participants.

### Intimate partner abuse (victimisation and perpetration) in the past 4 months

*The Abusive Behaviour Inventory Revised* (ABI-R) is a 25-item reliable tool to measure experiences of physical (13 items), psychological (9 items), and sexual abuse (3 items) victimisation and perpetration [36]. Each item can be scored from 1 (never) to 5 (very frequently). The higher the score on each subscale, the greater the frequency of abuse.

Controlling behaviours in relation to both perpetration and victimisation will be assessed using four adapted questions from the 24 item *Revised Controlling Behaviours Scale* (CBS-R) [53]: smash your partner’s property when annoyed/angry; want to know where your partner went and who they spoke to when not together; tell your partner they were going mad; and try to restrict time your partner spent with family or friends. Total score for the 4 questions ranges from 0 to 16; the higher the score, the greater the frequency of a partner using controlling behaviours.

*The Communications Patterns Questionnaire-Short Form* (CPQ-SF) [54] is an 11-item self-assessment of “spouses’ perceptions of marital interactions … to indicate the representativeness of that description for the conflict and communication patterns in their relationship”: male demand/female withdraw; female demand/male withdraw; original total demand/withdraw; alternate demand/withdraw; criticise/defend and positive interaction. Higher scores on each subscale suggest which communication pattern is likely to be used during conflict interactions.

Two scales (9 items) from *The Intimate Partner Violence Responsibility Attribution Scale* (IPVRAS) (included in the male baseline and follow-up questionnaires only) will assess perpetrators’ responsibility attribution to the victim (V) and responsibility attribution to the offender’s (i.e. perpetrator’s) personal context (O) [55]. The higher the score, the more responsibility attributed to the victim (V) or offender’s personal context (O).

The 12-item anger subscale from *The Propensity for Abusiveness Scale* (PAS) (included in the male baseline and follow-up questionnaires only) is included. The PAS predicts the perpetration of physical and emotional abuse. Scores on the anger subscale range from 12 (completely undescriptive of you) to 60 (completely descriptive of you) [56].

Two questions from a non-validated scale on the use of social media in relation to perpetration and victimisation of a partner will be included [57] (e.g. ‘Used mobile technology to check her location’). Total scores range from 2 (never) to 10 (very frequently); the higher the score, the greater the frequency of abuse using social media.

Four questions will be used from a non-validated scale to assess the use of children against a partner [35] (e.g. “Asked the children to report on what your current or former partner is doing or where she has been”). Total scores range from 4 (never) to 20 (very frequently); the higher the score, the greater the frequency of using children against a partner/the greater the frequency of having a partner use children against you.

There will be a question on the frequency of stopping a partner from leaving the house against their will/being stopped from leaving the house will be scored from 1 (never) to 5 (very frequently). Two questions on stalking behaviours scoring from 2 (never) to 5 (very frequently); the higher the score, the greater the frequency of experiencing or perpetrating stalking behaviour.

### Self-management

The 13-item *Brief Self-Control Scale* (BSCS) enquires about typical dispositional self-regulatory behaviours using two factors of self-control: restraint and impulsivity [58] (included in the male baseline and follow-up questionnaires only). Total scores range from 13 (not at all like me) to 65 (very much like me).

### Quality of life

*The ICEpop CAPability measure for Adults* (ICECAP-A) is used to assess a person’s well-being using a capability approach [59]. It has five attributes: **attachment** (an ability to have love, friendship, and support); **stability** (an ability to feel settled and secure); **achievement** (an ability to achieve and progress in life); **enjoyment** (an ability to experience enjoyment and pleasure), and **autonomy** (an ability to be independent), each with four levels of capacity. Tariff values range from 1 (full capability) to 0 (no capability).

*The EQ-5D-3L* consists of a descriptive system and a Visual Analogue Scale (VAS). The descriptive system assesses five dimensions of a person’s health state (mobility, self-care, usual activities, pain/discomfort, and anxiety/depression) on the day of administering, each with three response levels: no problems, some problems, and extreme problems [60]. The tariff index score based on the descriptive profile ranges from 1 (perfect health) to – 0.594 (worst health), with death anchored at 0 for the UK valuation set [61]. The EQ VAS records the respondent’s current self-rated health on a vertical visual analogue scale from 0 (worst imaginable health) to 100 (best imaginable health).

### Healthcare, social, and other legal and civil services use and criminal justice contacts

Participants’ utilisation of primary and secondary healthcare, social services, and other legal and civil services, including the prescribing of medication, and their contacts with criminal justice will be recorded retrospectively by self-report questionnaire.

### Experience of the group intervention (males allocated to the intervention arm, follow-up questionnaire only)

The 12-item *Working Alliance Inventory–Short Revised (WAI-SR) client version* measures three key aspects of therapeutic alliance: agreement on the tasks of therapy, agreement on therapy goals, and affective bond development [62]. *Scores range from 5 to 60,* with higher scores indicating a better therapeutic alliance between client and therapist. The patient version of the *California Psychotherapy Alliance Scale- Short Form* [63] has 12 items that measures the alliance in psychotherapy across 4 subscales: the patient working capacity, patient commitment, working strategy consensus, and therapist understanding and involvement. The total score is the mean of these four subscales.

The following will also be assessed and may be used as explanatory variables.

### Socio-demographic information

Data on participants’ relationship status, age, gender, ethnicity, highest education level attained, living arrangements, current employment status, number of children, and their living arrangements will be recorded.

### Childhood

The occurrence of ten *Adverse Childhood Experiences* (ACE) (e.g. physical, sexual, emotional abuse, neglect, household dysfunction) experienced before the age of 18 were assessed to produce an ACE score of cumulative childhood stress [64] (assessed in baseline questionnaire only). Scores range from 0 to 10; the higher the score the greater the childhood adversity experienced.

### Desirable responding

The *Balanced Inventory of Desirable Responding Short Form* (BIDR-SF) [65] (administered to male participants only). The BIDR-SF consists of two subscales: Self-Deceptive Enhancement (honest but overly positive responding) and Impression Management (bias toward pleasing others or ‘deliberate self-presentation’). Higher scores indicating more desirable responses. IPA scores will be adjusted for BIDR-SF scores.

### Motivation to change behaviour

*The URICA-Domestic Violence* (URICA-DV), administered to male participants only, is a 32-item measuring perpetrators’ readiness to end their violence [66]. URICA-DV includes four subscales to measure stages of change pre-contemplation, contemplation, action, and relapse. Responses are given on a 5-point Likert scale ranging from 1 (strong disagreement) to 5 (strong agreement).

#### Database systems

A web based electronic Case Report Forms system (InferMed MACRO) will be used to collect baseline and outcome data. The system is Good Clinical Practice compliant with full audit trail and database lock functionality and a range of validations will be programmed to minimise data entry errors. No data analysis will be undertaken until databases are locked.

Ten percent of coded questionnaires and 10% of entered data by site will be verified by the trial manager to check for errors. If coded questionnaires and data entered are found to contain errors, a further 10% will be checked.

#### Ethical issues

The trial will be conducted in compliance with the principles of the Declaration of Helsinki [67], the principles of Good Clinical Practice, and all of the applicable regulatory requirements (UK data protection laws (meaning the Data Protection Act 1998 until 24 May 2018, and from 25 May 2018 the European Union General Data Protection Regulation (GDPR) and applicable UK legislation that enshrines GDPR into UK law).

As part of the informed consent process, participants will be advised and provided guidance about confidentiality and the limits to it. Significant risk of future harm to self or others will be disclosed to their keyworker or the duty worker in the substance use service or the integrated safety service where the interview is taking place, or to the relevant authorities.

The trial may be prematurely discontinued by the Sponsor or Chief Investigator on the basis of new safety information or for other reasons given by the Data Monitoring and Ethics Committee/Trial Steering Committee, regulatory authority or ethics committee concerned. The trial may also be prematurely discontinued due to lack of recruitment or upon advice from the Trial Steering Committee. If the study is prematurely discontinued, active participants will be informed and no further participant data will be collected.

All serious adverse events resulting from participation in the trial will be reported to the Ethics Committee within 48 h of receiving the report.

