#### Sample size calculation

The sample size for a feasibility study should allow parameters required to inform the design of the definitive randomised controlled trial to be estimated. To estimate a standard deviation for a sample size calculation of a future evaluation trial, a sample of at least 50 participants is recommended [68]. Therefore, to recruit a sample size of 60 female current or former partners (i.e. 30 whose current or ex male partners in the intervention arm and 30 whose partners are in the control arm), and taking a conservative retention rate of 80% of female current or former partners at end of intervention assessment (4 months post-randomisation), we will recruit 76 female current or former partners. It is estimated that around 70% of current or former female partners will agree to take part in the trial, therefore approximately 108 male participants will need to be recruited to obtain a sample of 76 female current or former partners.

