#### Statistical analysis

This feasibility trial will estimate parameters needed for planning an efficacy trial including estimating various rates (e.g. recruitment, randomisation, follow-rates) and estimating the within-trial arm standard deviation, the pre-post correlation, and the Intracluster Correlation Coefficient (*ICC*) for possible outcome measures to inform the sample size calculation of a future randomised control trial. Outcome measures will be rated by the researcher for each participant for their suitability and acceptability and the mean scores summarised for each outcome. Outcome measures will be described by trial arm. Intervention effect sizes (e.g. incidence rate ratios for the count outcome and mean differences for continuous outcome measures) will be estimated for various outcome measures, but no formal hypotheses testing will be carried out.

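### If the trial is discontinued early for any reason, including poor recruitment, the plan ends all participant data collection, so those enrolled but not yet interviewed at 4 months give no post-baseline outcome data

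*Protocol article*

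**What the plan says.** The Ethical issues section gives the grounds for an early stop in two sentences. The first begins "The trial may be prematurely discontinued by the Sponsor or Chief Investigator on the basis of new safety information" and goes on to other reasons given by the oversight committees, a regulator or the ethics committee. The second is "The trial may also be prematurely discontinued due to lack of recruitment or upon advice from the Trial Steering Committee". A single consequence then covers all of them: on premature discontinuation, "active participants will be informed and no further participant data will be collected".

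The Follow-up section sets one post-baseline assessment: "Male and female participants will be followed-up at the end of the intervention (approximately 4 months post-randomisation"). Table 2 shows no other.

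The trial's purpose is to estimate design parameters. Feasibility measures states "The following feasibility parameters will be examined: rates of consent, recruitment, and follow-up by site and group allocation", and Statistical analysis adds "estimating the within-trial arm standard deviation, the pre-post correlation, and the Intracluster Correlation Coefficient" for possible outcome measures. Sample size calculation opens on the same aim: "The sample size for a feasibility study should allow parameters required to inform the design of the definitive randomised controlled trial to be estimated".

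**The concern.** The rule is explicit, so this is not a detail left to a fuller document. It also fits one of its own triggers badly. Slow recruitment is a foreseeable result in a feasibility trial, and nothing about it prevents interviewing people who are already in. If the trial were discontinued on that ground and the sentence followed, everyone still waiting for the 4-month interview would contribute baseline data only.

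What is at stake is the information that the trial was set up to give. The follow-up rate by site and arm, the pre-post correlation, and the post-baseline SD and ICC would all come from people whose interview happened to fall before the stop. Those are the earlier recruits. Because cycle 2 is to be informed by a formative evaluation of cycle 1 (Setting and participants), a stop during cycle 2 could remove most or all follow-up on the later implementation.

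**Working it through.** **Inputs, all from the protocol article**
- Target of 60 women with 4-month data, a cited minimum of 50 to estimate an SD, 80% retention of women, 70% partner uptake, 76 women and 108 men (Sample size calculation).
- 18 men per site/cycle stratum (Method of randomisation); three regions and two cycles (Setting and participants).
- First randomisation 17 July 2018, recruitment end 7 May 2019 (Trial status): 294 days.
- One follow-up at about 4 months, taken as 4 × 30.4375 = 121.75 days.

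**The plan's own figures reproduce**
- Women: 60 / 0.80 = 75. By arm, 30 / 0.80 = 37.5, rounded up to 38, and 2 × 38 = 76.
- Men: 76 / 0.70 = 108.6, and 108 × 0.70 = 75.6. Strata: 3 × 2 × 18 = 108.

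These figures do not test the stopping rule. They serve only to size what it would cost. The accrual patterns below are assumptions, because the document gives none.

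**Illustration A: accrual in cycles.** All 108 men are randomised and the trial stops with some of the last cycle still awaiting follow-up. Women with 4-month data = (108 − pending men) × 0.70 × 0.80.
- Near a cycle boundary: almost none pending, so about 60 women.
- 18 pending: 90 × 0.56 = 50.4.
- 36 pending: 72 × 0.56 = 40.3.
- 54 pending (a full cycle, 3 × 18): 54 × 0.56 = 30.2.

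**Illustration B: even, on-target accrual.** Men pending = (108 / 294) × 121.75 = 44.7 at any stop between month 4 and the end of recruitment, with 44.7 × 0.70 = 31.3 partners. Before month 4, everyone randomised is pending. After 7 May 2019 the number falls to zero over about 4 months.

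**Illustration C: slow, even accrual.** At half the planned speed, men pending = (54 / 294) × 121.75 = 22.4. The share pending does not depend on speed. At time t it is 4 months / t, so two-thirds at 6 months (4 / 6) and 41% at day 294 (121.75 / 294).

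**Precision of an SD.** The approximate relative standard error under normality is 1 / √(2(n − 1)).
- n = 60: 1 / √118 = 9.2%.
- n = 50: 1 / √98 = 10.1%.
- n = 30: 1 / √58 = 13.1%.

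The Sample size calculation counts women after 80% retention at the 4-month assessment, so the SD it sizes for is the one at follow-up.

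**The case against.** The strongest reply is that discontinuation is discretionary. The sponsor or the Trial Steering Committee could close recruitment and let follow-up finish, in which case the sentence never applies. A reader might infer that slow recruitment must trigger it, and the text does not say so. But the section names lack of recruitment as a ground for discontinuing the trial and does not mention the milder option. The ambiguity therefore stands and is worth removing.

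Second, after a safety stop it is not evident that more data collection is better. Partners are telephoned and interviewed (Recruitment), and couples who share a mobile phone are kept out to safeguard the woman (Inclusion and exclusion criteria). If the new information concerned research contact itself, ending contact could be protective. This stands, and the fix needs an exception for it.

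Third, a reader might infer that all harm information stops. The next paragraph of Ethical issues requires serious adverse events resulting from participation to go to the ethics committee within 48 h of receipt, and it sets no end at a stop. That sentence governs reporting of what arrives, not collection, so the position after a stop is unclear rather than settled.

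Fourth, part of the answer survives. Consent and recruitment rates do not need the 4-month interview, and baseline data already collected remain.

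**Conclusion.** The concern holds as a contingent design point. Following the rule as written would discard outcome data that could still be obtained, and no other section exempts the 4-month interview. It bears on men already randomised and partners already enrolled; only men are randomised, and partners are invited afterwards.

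The size is conditional on an early stop and on assumed accrual. It ranges from almost none pending near a cycle boundary to about 54 men with a full cycle pending, which leaves about 30 women against the target of 60 and the cited minimum of 50. On the SD alone that moves the relative standard error from about 9% to about 13%.

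The figure of about 45 men should not be read as the loss at any stop. It needs even, on-target accrual, which fits neither the two-cycle design nor a trial stopped for slow recruitment, and it applies only between month 4 and the end of recruitment. Nor do the documents support calling harm data the trial's purpose: the stated primary objective is feasibility, and harm data are a safety duty.

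**What to change.** Separate closing recruitment from terminating the study, and replace the sentence in Ethical issues with wording such as:

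> If recruitment is closed early or the trial is discontinued, men already randomised and partners already enrolled will be informed and invited to the planned 4-month interview, and adverse-event collection will continue to that point, unless they withdraw consent, or the reason for stopping or a direction from the ethics committee, DMEC or TSC rules out further research contact.

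Leave the rules for stopping the intervention as they are.

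The cost is about one sentence of protocol text and, if the trial does stop early, up to about 4 more months of interviews already planned for these participants. Because recruitment had begun, the change may need an ethics amendment and a check against the consent wording, which is not shown.
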